#### Statistical analysis

Data will be analysed using ANCOVA with the baseline score added as the covariate [41], with an alpha level of .05. Separate ANCOVAs will be completed to determine if the intervention group improved more than the control group at the end of training (at Week 11), and to determine if the intervention group had improved more than the control group after training had stopped for 3 months (at Week 24). The mean difference within group and the mean difference between groups and the associated 95% confidence intervals will also be calculated. To avoid bias and to maximize the randomization process, intention to treat analysis will be used. Where data are missing, the carry forward technique will be used, which assumes missing data remain constant [42].

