A student-led community-based PRT programme for young adults with Down syndrome is innovative and provides the supervision and social interaction people with Down syndrome need to exercise. Typically developing adolescents often exercise at a gym [30] and so this is a reasonable recreation option for adolescents with Down syndrome. Physiotherapy students make the ideal support people for adolescents with Down syndrome as they have an understanding of the principles of exercise training, and are close enough in age that the social relationship between the pair is meaningful. An additional beneficial outcome of this arrangement is that physiotherapy students have an opportunity to gain a unique experience of disability, something that is often missing from their professional training due to a lack of appropriate placements.

In summary, the published literature provides evidence that PRT can improve muscle strength and endurance in people with Down syndrome. There is now a need for a fully powered randomised controlled trial to investigate the effects of PRT on work task performance and level of physical activity for young adults with Down syndrome. We hypothesise that a community-based strength training programme will improve work task performance in adolescents and young adults with Down syndrome. The primary aim of this study, therefore, is to investigate if a community-based strength training programme can improve work task performance in adolescents and young adults with Down syndrome. The secondary aims are to investigate: (a) if the exercise programme leads to an improvement in muscle strength, and (b) if the exercise programme leads to an increase in the amount of moderate and vigorous level physical activity undertaken by adolescents and young adults with Down syndrome.

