#### Work task performance

The effect of the PRT programme on work task performance will be assessed using two tests (a) repetitive weighted box stacking and (b) weight carry test (pail carry). The repetitive weighted box stacking test requires the participants to repetitively lift 10 kg boxes, from the floor to a table 75 cm off the ground. The number of boxes stacked in one minute is measured. The weighted pail carry requires participants to carry two 20 litre buckets each weighing 10 kg around an oblong 10 m course marked with cones. The total distance covered in 30 seconds is measured in metres. Running is not permitted for safety reasons. These measures are recommended by the American College of Sports Medicine [33] and have demonstrated changes in people with intellectual disability [34,35].

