### Data analysis

#### Sample size estimation

Sample size is based on a predetermined difference in performance of a work task outcome measure (weighted box stacking) between the intervention and control group of 25% (equivalent to an increase of 1.27 weighted boxes stacked per minute). This is based on the amount of difference that is believed to be clinically important. Sample size calculations assumed a standard deviation of 1.75 boxes per minute [35] and indicated 35 participants would be needed in each group for power of 0.8, assuming 10% of participants would be lost to follow up.

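### The primary aim rests on two work tasks with neither named primary, each tested at .05, so an either-task claim at Week 11 carries a false positive rate of about 8-10% rather than 5%

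*Protocol article*

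**What the plan says.** The Background section states the aim as a construct, not as an endpoint: "The primary aim of this study, therefore, is to investigate if a community-based strength training programme can improve work task performance". Under Outcome measures, the construct is given two measures of equal standing: "work task performance will be assessed using two tests (a) repetitive weighted box stacking and (b) weight carry test (pail carry". The Abstract also lists the two side by side.

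The Statistical analysis section sets one rule for all outcomes: "Data will be analysed using ANCOVA with the baseline score added as the covariate [41], with an alpha level of .05". It adds that "Separate ANCOVAs will be completed to determine if the intervention group improved more than the control group at the end of training (at Week 11"; the same applies at Week 24. It gives no order of testing, no adjustment and no rule for combining the tasks.

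Under Sample size estimation, only one task is used: "Sample size is based on a predetermined difference in performance of a work task outcome measure (weighted box stacking". The difference is 1.27 boxes per minute, the SD is 1.75, power is 0.8 and loss is 10%, giving 35 per group. No time point is named there.

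The visits do have different purposes. The Outcome measures section uses Week 11 to establish the effect of the programme and Week 24 to see whether benefits last. The Research design section describes Week 24 in the same way.

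**The concern.** As written, either task can be put forward as the result that answers the primary aim, and that choice can be made after the data are seen. If one task is significant and the other is not, the article does not say whether the primary hypothesis is supported. The sample size assumes one decisive test, but the analysis section never says which test that is. The Discussion section expects the trial to give health professionals high-level evidence, so a positive primary claim should carry the 5% error rate that the article states.

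**Working it through.** **Inputs from the article.** Difference 1.27, SD 1.75, power 0.8, loss 10%, 35 per group, alpha .05, two tasks, two follow-up visits. The article does not state whether tests are one- or two-sided. Two-sided is assumed because it reproduces the sample size (step 1) and because the article plans 95% intervals: "The mean difference within group and the mean difference between groups and the associated 95% confidence intervals will also be calculated". The article gives no correlation between tasks or visits. The values below are assumptions and are shown as ranges.

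**Step 1: reproduce the stated sample size.**
- Normal approximation: n = 2(1.96 + 0.8416)² × 1.75² / 1.27² = 2 × 7.849 × 3.0625 / 1.6129 = 29.8, so 30 per arm. With loss, 30 / 0.9 = 33.3, so 34.
- Two-sample t-test: 30.8, so 31 per arm. With loss, 31 / 0.9 = 34.4, so 35. This matches the article exactly.
- One-sided .05 (normal approximation): 24 per arm, and 24 / 0.9 = 26.7, so 27. This does not match.

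The figure of 35 therefore belongs to one two-sided .05 test of box stacking.

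**Step 2: two tasks at Week 11, either may count.** The false positive rate under no effect is 1 − P(|Z₁| ≤ 1.96 and |Z₂| ≤ 1.96).
- Independent: 1 − 0.95² = 9.75%.
- Correlated (simulation, 4 million draws): 9.5% at correlation 0.3, 9.1% at 0.5, 8.4% at 0.7.
- Only results favouring training: 1 − 0.975² = 4.9% if independent, 4.8% at 0.3, 4.2% at 0.7, against 2.5% for one test.

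**Step 3: both visits may count (four tests).** This is a scenario that the article does not state.
- Independent: 1 − 0.95⁴ = 18.5%.
- Task correlation 0.3 with visit correlation 0.5: 16.9%.
- Task correlation 0.7 with visit correlation 0.8: 12.8%.
- Only results favouring training, same two settings: 8.5% and 6.4%.

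**Step 4: what each remedy costs.**
- One named primary test: 5% two-sided. The sample size is unchanged, and t-test power with 31 per arm is 0.803.
- Either task may count, Bonferroni at .025 each: 37 per arm, and 37 / 0.9 = 41.1, so 42 per group. By t-test it is 38 per arm, and 38 / 0.9 = 42.2, so 43 per group. At the present size, power falls to 0.71 (t-test, 31 per arm) or 0.74 (normal approximation, 35 × 0.9 = 31.5 per arm).

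**The case against.** The strongest reply is that the article already points to a lead test: the trial is sized on box stacking, and Week 11 is the visit meant to establish effects. This is largely right about the visits. A reader might infer from four tests at .05 that the error rate of the primary claim simply is 13-17%. The documents do not support that. Week 24 has a separate maintenance question, no any-of-four rule is stated, and the correlations are assumed. On the tasks the reply is weaker. Sizing on box stacking suggests a lead measure but does not bind the authors, since the article calls it only one work task measure among others.

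Second, no decision rule is stated at all. If both tasks had to succeed, the error rate would be at most 5%. That is true, so 8-10% is conditional on an either-task claim. But power for a both-task rule cannot exceed power for box stacking alone, and it is not established, because pail carry was not sized.

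Third, a result favouring control cannot support a claim of improvement. This stands: in that direction the rate is about 4-5%. The fair comparison is then 2.5%, so the inflation is still nearly twofold.

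Fourth, multiplicity detail may sit in an analysis plan that is not shown. The lack of a full testing scheme is therefore not the point. Which outcome decides the primary aim is a protocol decision, and the article fixes the aim, both measures, the alpha and the sample size without making it.

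A reader might also infer that the stated power and the stated alpha refer to different decisions. For the box-stacking comparison they refer to the same test, as step 1 shows. The gap is only that this test is not named as the primary one.

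**Conclusion.** The point holds in this form: one primary aim, two measures, neither named primary, each tested at .05 without order or adjustment, and a sample size that covers one of them. If either task at Week 11 can support the claim, the two-sided false positive rate is about 8-10%. This assumes two-sided tests and a task correlation between 0 and 0.7. Towards benefit only, it is about 4-5% against 2.5%. The range of about 13-17% (18.5% if independent) applies only if Week 24 may also carry the claim. It should be quoted only with that condition and with its assumed correlations of 0.3-0.7 between tasks and 0.5-0.8 between visits.

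**What to change.** Before unblinding, state that box stacking at Week 11, compared by baseline-adjusted ANCOVA at two-sided .05, is the single primary test. Treat pail carry at Week 11 and both tasks at Week 24 as secondary. If a formal claim on pail carry is wanted, it can be tested next in fixed sequence at .05, only if box stacking is significant. No further hierarchy is needed for this point.

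This takes a few sentences, restores 5% for the primary claim, and keeps 35 per group and 80% power for box stacking. The downside is that pail carry alone can no longer support the primary claim. If the sponsor wants either task to count, alpha must be split, and about 42-43 per group are needed to keep 80% power for box stacking; otherwise power of about 0.71-0.74 must be accepted.

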## Methods

### Research design

This randomised controlled trial will compare the effect of a 10-week student-led community-based PRT programme compared with a social programme. Specifically, this trial will examine if a student-led PRT programme improves work task performance and muscle strength in adolescents and young adults with Down syndrome and if it leads to improved activity levels after the programme has been completed. Seventy adolescents and young adults with Down syndrome will be recruited.

The trial has received ethics approval from the La Trobe University Human Ethics Committee and from the Victorian Department of Education and Early Childhood Development. Written informed consent will be sought from the next of kin (parent or guardian) of all adolescents with Down syndrome aged 14 to 17 years. The adolescents with Down syndrome will also be invited to provide their own written assent to participate in the study. For young adults with Down syndrome aged between 18 and 22 years, competence to give consent will be determined in conjunction with their next of kin. Where a young adult usually provides their own consent, they will provide their own informed consent for participation in this study. Where a young adult has been determined by their next of kin to not be cognitively able to provide their own consent, informed consent will be sought from the next of kin. In this case, the young adult will also be invited to provide their own written assent.

All participants will complete a baseline assessment after which they will be randomly allocated to either the intervention or control group. Following a 10-week period of training for the intervention group and a programme of social activities in the control group, all participants will be reassessed at Week 11. All participants will then continue with their usual activities for 3 months; at Week-24 both groups will complete a follow-up assessment to establish if any of the benefits of the programme have been maintained.

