### Outcome measures

All outcome measures will be assessed at baseline (Week 0), immediately post intervention (Week 11) to establish the effects of the programme and 3-months post-intervention (Week 24) to determine if the benefits of the intervention are maintained. All assessments will be completed by an assessor who is blind to group allocation and who has no involvement in recruitment, the randomisation procedure, or the training programme.

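### Carry-forward is the only stated rule for missing scores; it assumes no change after loss, and which way it biases Weeks 11 and 24 depends on who is lost and when

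*Protocol article*

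**What the plan says.** The Statistical analysis section of the protocol article sets the model: "Data will be analysed using ANCOVA with the baseline score added as the covariate [41], with an alpha level of .05". One such model is fitted at Week 11 and a separate one at Week 24. On the analysis set it states: "To avoid bias and to maximize the randomization process, intention to treat analysis will be used". On missing scores it states: "Where data are missing, the carry forward technique will be used, which assumes missing data remain constant". The article gives no other missing-data method and no sensitivity analysis.

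The purpose of the last visit appears twice. Under Research design, "at Week-24 both groups will complete a follow-up assessment to establish if any of the benefits of the programme have been maintained". Under Outcome measures, the visit is "3-months post-intervention (Week 24) to determine if the benefits of the intervention are maintained".

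The Sample size estimation section expects some loss, "assuming 10% of participants would be lost to follow up", without saying when it falls or from which arm.

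**The concern.** Carry-forward sets all change after the last observed visit to zero. In a three-visit trial this has two different consequences.

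- **Lost between Week 11 and Week 24.** The Week 11 score is reused at Week 24. For that person the plan assumes that whatever was gained is fully kept, although the Week 24 visit exists to find out whether it is.
- **Lost before Week 11.** The baseline score is used at Week 11 and again at Week 24. A participant in the progressive resistance training (PRT) arm is credited with no training gain, and a participant in either arm with no practice gain. The outcome value is then identical to the covariate in the ANCOVA.

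In both cases one imputed number enters the model as though it had been measured, with no allowance for its uncertainty. The rule can bias the group contrast even when loss is completely at random. At stake are the Week 11 comparison, which addresses the primary aim, and the Week 24 conclusion about maintenance.

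**Working it through.** **Inputs from the article (Sample size estimation).** Effect 1.27 boxes per minute, SD 1.75, 35 per group, power 0.8, 10% loss. Two-sided alpha is assumed, in line with the 95% intervals.

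**The plan's own figure.** A two-sample t calculation for 1.27 with SD 1.75 gives 30.8, so 31 per group. 31 / 0.90 = 34.4, so 35. The stated sample size reproduces.

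**Formulas.** Let *e* be the share lost before Week 11, *l* the share lost between Week 11 and Week 24, and E11 and E24 the true effects. Randomisation balances the baseline, so the adjusted contrast has the same expectation as the difference in follow-up means. With equal random loss in both arms, and dropouts who would have fared as completers did:

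- Week 11 estimate = (1 − e) × E11
- Week 24 estimate = (1 − e − l) × E24 + l × E11

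A gain common to both arms cancels when loss is equal. It does not cancel when loss is unequal, so the last two rows assume a common gain of 0.5 boxes; the article gives no figure for it. The timing and split of loss and the value of E24 are also assumptions. Ten per cent of 35 is 3.5 people, so 4/35 (11.4%) is shown beside 10%.

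| Scenario | Arithmetic | Carry-forward | True |
|---|---|---|---|
| Week 11, 10% early | 0.90 × 1.27 | 1.143 | 1.27 |
| Week 11, 4/35 early | 31/35 × 1.27 | 1.125 | 1.27 |
| Week 24, E24 = 0, 10% late | 0.10 × 1.27 | 0.127 | 0 |
| Week 24, E24 = 0, 4/35 late | 4/35 × 1.27 | 0.145 | 0 |
| Week 24, E24 = 0, 2/35 early and 2/35 late | 2/35 × 1.27 | 0.073 | 0 |
| Week 24, E24 = 0.635, 10% late | 0.90 × 0.635 + 0.10 × 1.27 | 0.699 | 0.635 |
| Week 24, E24 = 0.635, 10% early | 0.90 × 0.635 | 0.572 | 0.635 |
| Week 24, E24 = 1.27, 4/35 early | 31/35 × 1.27 | 1.125 | 1.27 |
| Week 24, E24 = 1.27, 4/35 late | (31/35 + 4/35) × 1.27 | 1.27 | 1.27 |
| Week 11, 6/35 PRT and 2/35 control early | 29/35 × 1.77 − 33/35 × 0.5 | 0.995 | 1.27 |
| Week 11, no PRT and 20% control early | 1.77 − 0.80 × 0.5 | 1.37 | 1.27 |

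**Simulation of the planned ANCOVA.** 8,000 trials per scenario, baseline mean 5.08 (= 1.27 / 0.25), baseline/follow-up correlation assumed between 0 and 0.7.

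- **Week 11, 10% lost early from both arms:** estimate about 1.14, against 1.27 from observed scores. Power is 0.76 against 0.80 (correlation 0), 0.88 against 0.90 (0.5) and 0.97 against 0.98 (0.7).
- **Week 11, 6/35 PRT and 2/35 control lost early:** estimate 0.99–1.00. Power is 62, 68 and 84% at correlations 0, 0.3 and 0.6, against 79, 82 and 94% from observed scores.
- **Week 24, no true effect, about 10% lost late:** type I error about 6–7%; observed-score ANCOVA stays at 4–5%.
- **Week 24, no true effect, 2/35 early and 2/35 late:** type I error 4.8–5.4%, essentially nominal.

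**The case against.** The best defence is that the effect is small at the loss the plan expects. About 0.13 boxes is 0.13 / 1.75 = 0.07 SD, and only three or four people per arm are imputed. The single 10% figure also cannot fall wholly before and wholly after Week 11, so the two worst cases do not add up. This stands, and it limits the severity.

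It is also fair that the Week 11 dilution is conditional. If people who stop training truly gain nothing, a zero gain is right for an effect that counts everyone as randomised, and nothing is diluted.

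A reader might infer four stronger points, which the article does not support:

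- **That Week 24 is always tilted towards maintenance.** It is not. People lost before Week 11 carry baseline to Week 24 and pull the estimate down.
- **That the rule contradicts the trial's own hypothesis that gains fade.** The Background hypothesises only that training improves work task performance. Maintenance is left open, and the Discussion suggests that participants may go on exercising.
- **That the rule conflicts with the sample size.** Recruiting extra people to allow for loss and then imputing is not contradictory, and 35 per group reproduces.
- **That accelerometer data returned by post will be missing more often.** This is conceivable, but the Physical activity section gives no loss rate.

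A separate analysis plan may exist. The article does not leave the matter open, however: it names the method and its assumption, so a later plan would have to reverse the sentence.

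**Conclusion.** The concern holds in a limited form and should be fixed; it does not undermine the design. Carry-forward assumes retention for those lost late and no gain for those lost early. The sign and size of the bias therefore depend on when participants leave and from which arm, and the rule cannot be defended as conservative.

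With equal random loss near 10% the bias is modest: up to about 0.15 boxes at either visit, and at most one to two percentage points of type I error at Week 24, falling to almost none if loss is spread evenly over the two periods. Unequal loss matters more. About 11% overall, split 6/35 against 2/35 before Week 11, takes the Week 11 estimate to about 1.0; loss only from an improving control arm would inflate it instead.

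These sizes rest on the plan's effect and SD, on dropouts who would have behaved as completers did, and on assumed timing, correlation, common gain and Week 24 effect.

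**What to change.** Replace the carry-forward sentence with a primary analysis that is valid under missing-at-random and uses every observed visit. Either of two options would do:

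- a likelihood-based repeated-measures model with baseline adjustment, giving the group contrast at Week 11 and at Week 24; or
- multiple imputation using all visits, followed by the two ANCOVAs already planned.

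Report both contrasts with 95% confidence intervals. Add one sensitivity analysis for departures from missing-at-random. Carry-forward may stay as a secondary analysis labelled as such.

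The cost is a change of wording and slightly more analysis work, with no new data or participants. The price is reliance on missing-at-random, which the sensitivity analysis probes. The change should be made before outcome data are seen, so that it cannot look data-driven.

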## Discussion

This paper outlines the study protocol for a randomised controlled trial on the effects of progressive resistance training for adolescents and young adults with Down syndrome. It will establish if a novel, student-led community based PRT programme can improve work task performance and physical activity levels of young adults with Down syndrome. The trial is novel as it incorporates a student-mentor component designed to overcome some of the difficulties associated with participation in exercise for people with Down syndrome and encourages community participation as the training will take place at a local facility. The student mentor approach provides the programme with a potentially sustainable way of providing supervision for adolescents with Down syndrome when exercising.

If successful, PRT could be a feasible, meaningful, enjoyable and realistic recreation option for adolescents with Down syndrome as they make the transition to adulthood. This initial period of training may also give them the confidence to continue exercising after the trial finishes. The intervention addresses the impairment of muscle weakness which is likely to diminish their work task performance. It also has the potential to increase their physical activity levels in the short term and to decrease their risk of the secondary health consequences of inactivity in the long term.

This trial has the potential to make a significant difference to the health and employability of the more than 1 million people with Down syndrome worldwide. The trial outcomes will also impact on clinical practice by providing high level evidence to health professionals who work with people with Down syndrome about whether exercise programmes are effective for this group. If young adults with Down syndrome do become stronger and more physically activity, it may enable them in the short term to be more active in their school, work and home communities. The trial may also have long-term impact on the health of adults with Down syndrome, by providing them with an exercise option that will improve their work performance and lessen their risk of developing the secondary health consequences of inactivity.

